## Abstract

**Background:**

Persistent disability in chronic stroke survivors is often attributed to arm or leg weakness; however, respiratory muscle weakness also impedes poststroke rehabilitation, reduces quality of life, and increases the risk of health complications. Respiratory complications are common after stroke and place patients at risk for both prolonged functional disability and mortality. In addition, stroke survivors face ongoing cardiovascular disease that places them at risk for recurrent stroke.

**Objective:**

The study aims to compare the effects of 2 respiratory training programs, paired with individualized flexibility, strengthening, and cardiovascular exercise programs, on physiologic, activity, and societal participation outcomes in chronic stroke survivors.

**Methods:**

This study will be a randomized controlled trial. Participants are 80 community-dwelling adults with chronic stroke. In conjunction with a 24-session (3 times/week for 8 weeks), American Heart Association–informed, whole-body exercise program, participants will be randomized to receive either respiratory strength training or respiratory relaxation training. Study intervention will be directed by a physical therapist and take place in a community fitness center. Outcome assessments will occur in a clinical research center. The primary outcome measure is maximal respiratory pressure. Secondary outcome measures include airway clearance, walking endurance, spatial-temporal gait characteristics, community walking, functional strength and fatigue, depression, and societal participation measures. Longer-term societal participation is a complex domain that may be influenced by other factors beyond physical function. Participants’ health status will be monitored for 1 year following the intervention for falls, respiratory illness, and hospitalizations. Additional subanalyses will evaluate the effect of smoke exposure on short- and long-term outcomes. Outcome assessors are blinded to group assignments. Respiratory relaxation training is an active comparator, but no pure control group is included.

**Results:**

This study was funded in March 2020 with enrollment commencing in November 2020. Completion of enrollment is projected for May 2025 with a study projected end date of April 2026. Published results are anticipated in Fall 2026.

**Conclusions:**

Results from this study will improve our understanding of the additive benefits of respiratory exercises on short- and long-term physiologic, functional, and societal gains for these individuals. These data will be instructive to meet a current unmet rehabilitative need to promote patient-centered care and contribute to decreasing morbidity and mortality in chronic stroke survivors.

**Trial Registration:**

ClinicalTrials.gov: NCT05819333; https://clinicaltrials.gov/study/NCT05819333

**International Registered Report Identifier (IRRID):**

DERR1-10.2196/59749

## Introduction

### Background

Stroke is the leading cause of serious long-term disability in the United States [1]. A decrease in stroke mortality (36.9% decrease from 1999 to 2009), has led to a subsequent increase in those living with the consequences of stroke [2]. As such, it impacts the financial status of patients, families, and health care systems [3]. A retrospective study of inpatient stroke care costs from 2000 to 2020 revealed mean hospital costs per stay were US $15,781 (SD US $330) [4]. The mean lifetime cost of ischemic stroke is approximately US $140,048 in the United States, placing stroke among the top 10 most costly conditions among Medicare beneficiaries [5]. Recurrent stroke, cardiac disease, and respiratory complications are the leading causes of mortality in stroke survivors. Given these financial and health costs, there is therefore a critical need to prevent further cardiovascular and cardiorespiratory decline and reduce the incidence of cardiac and respiratory disease and functional disability.

Although stroke sequelae affect numerous body systems, automatic control of resting ventilation is typically spared in the majority of stroke cases, affected only in more severe brainstem strokes. Motor deficits are often the most debilitating to mobility and return to participation in life roles. Motor processing and the voluntary control of muscles of respiration engaged when speaking, upon exertion, coughing, or with exercise may be weakened following damage directly to the cerebral cortex or the descending axonal projections. Consequently, individuals after stroke may exhibit prolonged exercise intolerance, dyspnea, and airway clearance dysfunction. It is upon this conceptual framework we propose that respiratory muscle training is an important component in the rehabilitation of individuals following stroke. The purposes of this study are to (1) evaluate the effect of a combined exercise program (EP) with respiratory strength training (RST) on measures of impairment, activity, and participation; (2) evaluate its ability to maintain prospective respiratory health; and (3) explore the effect smoking history may have on these outcomes.

### Study Objective and Aims

The primary objective of this trial is to test the hypothesis that a combined EP with RST improves physiologic, activity, and societal participation outcomes in chronic stroke survivors. In addition to limb and respiratory weakness, up to 78% of patients after stroke present with dysphagia [6], a significant risk factor for aspiration. Cough is a critical mechanism to guard against aspiration and is often impaired after stroke [7], resulting in greater incidences of aspiration and chest infection [8,9]. Furthermore, pneumonia is the leading cause of nonvascular death in acute [10] and chronic [11] phases after stroke. RST could improve airway clearance as a protective function. The adoption of interventions capable of preventing the occurrence of respiratory complications may substantially improve the long-term outcomes of these patients [12]. Several small-scale studies have demonstrated that inspiratory [13-16] and expiratory [14] muscles respond to strength training in patients after stroke, but the impacts of respiratory strengthening on function are less clear. In a systematic review of poststroke respiratory muscle training randomized controlled trials, Menezes et al [17] reported there were insufficient data to determine whether the benefits of respiratory muscle training are realized in gains in functional activity level or participation, concluding that future trials are needed to assess the effects of training on one’s activity and participation in life roles. RST for individuals after stroke has the potential to facilitate a return to these important societal roles.

Our secondary objective is to prospectively monitor health status for 1-year following the exercise intervention. There is a clear link between the presence of respiratory dysfunction in individuals after stroke and the incidence of respiratory complications such as aspiration or respiratory infections [18-20]. Menezes et al [17] revealed that respiratory muscle training reduced the relative risk of respiratory complications immediately and 6 months after the commencement of the intervention. Others have reported that expiratory muscle strength training exercises improve respiratory strength, cough, and swallowing function in stroke [21-23]. A 2016 meta-analysis [17] revealed that respiratory muscle training reduced the relative risk of respiratory complications immediately and 6 months after the commencement of the intervention. However, this conclusion was based on just 2 trials, and procedures for detecting the occurrence of respiratory complications were not sufficiently robust.

An exploratory objective will evaluate potential differential responses to respiratory muscle training based on smoke exposure. Cigarette smoking negatively impacts respiratory health and increases the risk of cardiovascular events. While direct cigarette smoking is a known risk factor for stroke and poststroke complications, individuals exposed to secondhand smoke also face high health risks. There is a strong, dose-dependent association between passive smoking and stroke [24].

## Methods

### Trial Design

This is a single-blind randomized controlled trial. Participants will be assessed at Brooks Rehabilitation Clinical Research Center and receive intervention sessions at the Brooks Family YMCA. Health status will be monitored monthly for 1 year following the intervention. This study is registered at ClinicalTrials.gov (NCT05819333). The trial will be reported according to SPIRIT (Standard Protocol Items: Recommendations for Interventional Trials), TIDieR (Template for Intervention Description and Replication), and CONSORT (Consolidated Standards of Reporting Trials) guidelines (Figure 1).

**Figure 1 figure1:**
[figure not shown]
Flowchart of clinical trial. EP: exercise program; RRT: respiratory relaxation training; RST: respiratory strength training.

### Ethical Considerations

This protocol and Informed Consent Form were reviewed and approved by the University of Florida’s institutional review board (IRB; #202000810). Participants will sign the IRB-approved informed consent form before enrollment. Participants will be assigned a unique numerical identifier to deidentify and assure the privacy and confidentiality of all collected data. Compensation of US $15/study visit will occur in the form of a debit card, with a total compensation of US $405.

To evaluate not simply how many steps participants take but to understand where those steps are taken (ie, within the confines of their home or actually outside their home in the community), participants will wear a GPS device for 7 days. These deidentified longitude and latitude coordinate data are not collected in real-time but rather will be downloaded to a password-protected computer at the completion of the 7-day wearing period. Safety of trial intervention and assessments will be monitored by reporting to the IRB any adverse events that occur from enrollment to trial completion at 12 months following the intervention.

### Participants

Participants will be recruited from an IRB-approved clinical research registry and study flier. Power calculations determined a study population of 80 participants and are presented below. We will enroll up to 95 participants to allow for a potential attrition rate of up to 15% (14/95). Specific inclusion and exclusion criteria for study enrollment are presented in Textbox 1. The cardiovascular and respiratory exclusion criteria were adopted from a previous exercise study with individuals poststroke [25,26].

Inclusion and exclusion criteria for enrollment into the trial.
**Inclusion criteria**
Diagnosis of stroke >6 months after onsetSigned letter of medical approval from primary care physician to participateCommunity dwellingAbility to attend the exercise program 3 times/week for 8 weeksAbility to follow directions or mimic exercisesAbility to communicate adverse effects such as pain or fatigue or the need for assistanceAble to ambulate 20 feet (6.1 m) with no more than contact guard assist, with or without an assistive device or orthotic deviceAble to access exercise equipment independently or with caregiver assistOlder than 18 years of age
**Exclusion criteria**
Neurologic conditions other than stroke (ie Parkinson disease or multiple sclerosis)Severe, functional limiting arthritisOrthopedic condition that limits mobilitySevere weight-bearing painCurrent participation in other physical rehabilitation services or exercise programsSerious cardiac conditions (hospitalization for myocardial infarction or heart surgery within the past year, history of congestive heart failure, documented serious and unstable cardiac arrhythmias, hypertrophic cardiomyopathy, severe aortic stenosis, angina or dyspnea at rest or during activities of daily living). Anyone meeting New York Heart Association criteria for Class 3 or Class 4 heart disease will be excluded.Severe hypertension with systolic >200 mm Hg and diastolic >110 mm Hg at rest, that cannot be medically controlled into the resting range of 180/100 mm HgUse of supplemental oxygenSevere obstructive pulmonary disease (Classification of Global Initiative for Chronic Obstructive Lung Disease 3 or higher, indicating forced expiratory volume 1 <50% predicted)Treatment for pneumonia or lower respiratory infection within the past monthAble to run one-quarter mile (402 m) without stopping

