#### Cardiovascular Exercise

Exercise modalities may include treadmill, recumbent cross trainer, recumbent bicycle, stairs, elliptical stepper, upper-extremity ergometer, arc trainer or provided through overground gait, sit-to-stand repetitions, shallow knee bends, step-ups, and marching in place.

In terms of progression, participants will wear a heart rate monitor and exercise between 40% and 70% of heart rate reserve. The exertion will be subjectively reported using the rate of perceived exertion scale [28]. Progression will occur by increasing exercise duration, resistance, or speed.

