## Results

This study was funded in March 2020 with enrollment commencing November 2020. As of July 2024, a total of 69 participants were enrolled. Completion of enrollment is projected for May 2025 with a study projected end date of April 2026. Published results are anticipated in Fall 2026.

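### As worded, the severe hypertension exclusion needs both resting limits to be exceeded, so an uncontrollable 215/100 or 190/115 does not meet it while 205/112 does

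*Protocol article*

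**What the plan says.** In the protocol article, Textbox 1 (Exclusion criteria) excludes people whose severe hypertension is given as "systolic >200 mm Hg and diastolic >110 mm Hg at rest, that cannot be medically controlled into the resting range of 180/100" mm Hg. The criterion thus has three parts: a systolic limit, a diastolic limit joined to it by 'and', and failure of medical control.

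The Participants section explains where it came from: "The cardiovascular and respiratory exclusion criteria were adopted from a previous exercise study with individuals poststroke".

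Three other places bear on the same risk, none with a blood pressure figure:

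- The inclusion criteria require a signed approval letter from the primary care physician.
- The EP Components section has the physical therapist direct the exercise and fit it to the individual.
- The Cardiovascular Exercise section says that "participants will wear a heart rate monitor and exercise between 40% and 70% of heart rate reserve", with perceived exertion also recorded.

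On recruitment, the Results section states: "As of July 2024, a total of 69 participants were enrolled". The Participants section sets the target at 80 and the ceiling at 95.

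**The concern.** A severe hypertension exclusion should remove the people at highest risk before exercise begins. Read literally, this one does not rank people by risk. It removes 205/112 but not 190/115, where the diastolic is higher, nor 215/100, where the systolic is higher. A person with only one pressure above its limit stays outside the exclusion even if treatment cannot bring it down.

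The literal reading is a reasonable one for a screener. Elsewhere in the same list, conditions that each exclude on their own are joined by 'or', as with pneumonia and lower respiratory infection, or the two New York Heart Association classes. 'And' in the hypertension item therefore naturally reads as 'both'.

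What is at stake is participant safety and consistent screening. Participants are stroke survivors who will do resistance and aerobic exercise and, in one arm, loaded breathing at maximal volume and speed.

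**Working it through.** **Step 1: the rule as logic.** Write S and D for resting systolic and diastolic pressure in mm Hg.

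- As worded: exclude if (S > 200 and D > 110) and the pressure cannot be controlled to 180/100.
- With 'or': exclude if (S > 200 or D > 110) and the pressure cannot be controlled to 180/100.

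Applied to four readings that cannot be controlled:

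| Reading | S > 200 | D > 110 | Excluded as worded | Excluded with 'or' |
|---|---|---|---|---|
| 215/100 | yes | no | no | yes |
| 190/115 | no | yes | no | yes |
| 205/112 | yes | yes | yes | yes |
| 195/105 | no | no | no | no |

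The first two readings miss the criterion's own control target (215 > 180; 190 > 180 and 115 > 100), yet the rule as worded does not catch them.

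**Step 2: is the gap closed elsewhere?** The item on serious cardiac conditions does not list hypertension. The physician's letter carries no stated threshold. Exercise intensity is set by heart rate reserve and perceived exertion. No other part of the article states a blood pressure limit.

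**Step 3: how many people could it touch?** The article gives no blood pressure distribution, so the following inputs are assumptions: resting pressure is bivariate normal, with three sets of means and SDs and a correlation r of 0.5 or 0.8.

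P(exactly one limit exceeded) = P(S > 200) + P(D > 110) − 2 × P(both exceeded).

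Share with only one limit exceeded = P(exactly one) / [P(exactly one) + P(both)].

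| Scenario | Systolic mean (SD) | Diastolic mean (SD) | P(S > 200) | P(D > 110) | r | P(both) | P(exactly one) | Share with only one |
|---|---|---|---|---|---|---|---|---|
| A | 135 (20) | 78 (11) | 0.00058 | 0.00181 | 0.5 | 0.00005 | 0.00228 | 98% |
| A | 135 (20) | 78 (11) | 0.00058 | 0.00181 | 0.8 | 0.00025 | 0.00189 | 88% |
| B | 140 (22) | 82 (13) | 0.00319 | 0.01563 | 0.5 | 0.00074 | 0.01733 | 96% |
| B | 140 (22) | 82 (13) | 0.00319 | 0.01563 | 0.8 | 0.00211 | 0.01460 | 87% |
| C | 145 (25) | 85 (14) | 0.01390 | 0.03707 | 0.5 | 0.00391 | 0.04317 | 92% |
| C | 145 (25) | 85 (14) | 0.01390 | 0.03707 | 0.8 | 0.00902 | 0.03294 | 79% |

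For example, scenario C with r = 0.5: z = (200 − 145)/25 = 2.20 gives 0.01390; z = (110 − 85)/14 = 1.79 gives 0.03707; and 0.01390 + 0.03707 − 2 × 0.00391 is about 0.0432. The table rounds each entry from unrounded values.

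Enrolments remaining after July 2024: 80 − 69 = 11 to the target, or 95 − 69 = 26 to the ceiling.

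- To the target: 11 × 0.00189 = 0.02 to 11 × 0.04317 = 0.47 people.
- To the ceiling: 26 × 0.00189 = 0.05 to 26 × 0.04317 = 1.12 people.

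These counts are on the high side for each scenario, because they do not remove people whose pressure can be controlled to 180/100 or whom the physician declines to approve.

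**The case against.** The best defence is that 'and' merely lists the two limits. Blood pressure is recorded as a pair, and the same sentence gives its control target as a pair. On that reading nobody would admit an uncontrolled 215/100, and nothing in the article shows that anyone has. Alternatively, 'and' may be deliberate: the same list uses it in that sense for arrhythmias that must be both serious and unstable. The wording may also have come from the earlier study, and neither that study nor the full protocol and screening form is shown. The physician's letter, the separate cardiac exclusions, therapist supervision, the heart rate limits and adverse event reporting all lower the risk. The counts rest on assumed distributions and vary more than twentyfold. Finally, 195/105 stays eligible under either wording, and a late change of eligibility may need an ethics amendment.

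Much of this stands, and it holds the point at the lowest level of importance. It does not remove the point. The article states the criterion in full, so this is not a detail left to another document. A threshold that two trained screeners can apply differently is badly fixed, whatever its origin. A deliberate both-limits rule would be hard to square with a control target that an excluded and a non-excluded person can both fail. The safeguards reduce the risk without correcting the rule. The eligibility of 195/105 follows from the limits the trial chose and is a separate matter.

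**Conclusion.** The point holds as a minor wording defect in a safety criterion. The logic in Step 1 needs no assumption beyond reading 'and' literally. Its practical size does rest on assumptions: under the distributions tried, exactly one limit is exceeded by 0.2% to 4.3% of people, which is probably at most about one of the remaining enrolments. Among people above at least one limit, 79% to 98% exceed only one, so in every scenario the literal rule misses most of those it appears meant to catch. Not meeting this exclusion is not the same as being admitted, since the physician's letter is still required. There is no effect on sample size, power or analysis. Whether the full protocol or screening form has the same wording cannot be seen from the article.

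**What to change.** In Textbox 1 and on the screening form, replace 'and' with 'or': exclude resting systolic pressure above 200 mm Hg or diastolic pressure above 110 mm Hg that cannot be medically controlled to 180/100 mm Hg or below. If the full protocol or screening form already says 'or', only the article needs correcting.

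The cost is one word, about 0 to 1 extra exclusions among the remaining enrolments under the assumptions above and, if the operative protocol says 'and', at most a routine ethics amendment. The last participants would then be screened under a slightly stricter rule than the first 69. If enrolment has closed, correcting the article still helps anyone who reuses the criterion.

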### Randomization, Allocation, and Blinding

Participants will be randomized to the EP plus RST group or EP plus respiratory relaxation training (RRT group) using the Microsoft Excel (Microsoft Office Professional Plus 2016) *RAND* function. Participants and the intervention physical therapist will be aware of the group assignment due to the nature of the intervention; however, study evaluators will remain blinded.

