### Data Analysis

#### Power Calculations

Our primary outcome measure is MIP. The power calculation was based on work by Messaggi-Sartor et al [14], who examined the effect of RST on respiratory strength and respiratory complications following subacute stroke and measured MIP as the primary outcome. MIP mean gain was 18.9 (SD 15.1) cm H_2_O in the experimental RST group and the mean MIP change was 9.3 (SD 10.1) cm H_2_O in the control (sham RST) group. With a total of 80 participants (40 in each group) in this study, a 2-sided repeated measures ANOVA comparing 2 treatments across 3-time points, using a pooled SD of 12.8 would detect a difference at power >0.8 (f=0.16, F=3.067, =0.5, =.5). For our secondary objective, the RST effect on lung infections may be even more robust. Messaggi-Sartor et al [14] reported a 70% lower lung infection rate for subjects who completed RST during subacute stroke rehab, compared with subjects allocated to the control group. The number needed to treat to prevent one lung infection event was seven [14]. The effect of RST on respiratory complications for those with chronic stroke is not yet known. Our exploratory objective is to distinguish responses to RST, based on smoking exposure. The primary intent of this objective is to collect data to power a future, larger study. Specifically, baseline function is lower in current smokers without neurological disease, and their tolerated exercise training volume may be reduced. A sample size of 80 will provide an opportunity to evaluate whether smoking influences responses to the exercise interventions.

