## Discussion

### Anticipated Findings

Results from this study will improve our understanding of the additive benefits of respiratory exercises on short and long-term physiologic, functional, and societal gains for these individuals. We hypothesize that the combined RST+EP will be more effective than the EP alone for stroke survivors with and without a smoking exposure history. Specifically, we hypothesize that combined RST+EP will be more effective in restoring poststroke maximal respiratory pressure, in restoring both physical (walking endurance) and respiratory (airway clearance) function, and in restoring poststroke life and social roles. We also hypothesize that RST+EP will be more effective than EP alone in reducing 1-year postintervention incidence of adverse respiratory events.

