### Limitations

We recognize some limitations of the study design. The study was powered to distinguish the 8-week effects of RST from RRT on MIP. We acknowledge that societal participation is multidimensional, and longer-term changes may be influenced by many contributing factors beyond respiratory strength and walking endurance [77,78]. The use of patient-reported outcome measures and assessment of the Area Deprivation Index will help identify some factors that contribute to societal participation. Since group assignment will be based on the type of respiratory training, it is possible there may be unequal proportions of smoke-exposed and nonsmoking participants in each group. The monitoring of smoke exposure will enable us to explore whether the combined respiratory and whole-body exercise approaches offer distinct benefits to cigarette smoke-exposed individuals. While study assessors will be blinded to group assignment, patients and exercise supervisors will know their respiratory exercise assignment. A true control or “sham” respiratory training intervention was not included; rather, the RRT serves as an active comparator. The volume of respiratory exercises during exercise sessions will be the same for both groups, even though the physiological effects of RST and RRT exercises likely differ.

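### The article foresees unequal smoke exposure between the arms, yet the between-arm model does not adjust for it

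*Protocol article*

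**What the plan says.** Randomization, Allocation, and Blinding names the tool, "using the Microsoft Excel (Microsoft Office Professional Plus 2016) *RAND* function", and mentions no stratification factor. Limitations states that "it is possible there may be unequal proportions of smoke-exposed and nonsmoking participants in each group", and gives as the reason that assignment follows the type of respiratory training.

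Other sections say why smoke exposure matters:
- Power Calculations says that current smokers (without neurological disease) have lower baseline function and may tolerate less training.
- Effects of Smoke Exposure links chronic exposure to greater work of breathing, dyspnea and impaired airway clearance.
- Anticipated Findings states the main hypothesis, that the combined program will be "more effective than the EP alone for stroke survivors with and without a smoking exposure history".

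Exploratory Objective Outcomes already sorts every participant into one of two exposure categories from a urine cotinine test.

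Statistical Analysis describes one mixed effects model for all objectives. Its listed terms are the baseline value (depending on the outcome), the intervention effects at 4 and 8 weeks, age, gender and BMI. Smoke exposure is not listed.

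**The concern.** A factor that the authors expect to influence response, and expect may differ between arms, can be balanced by stratified allocation or adjusted for in the model. The article describes neither. The factor bears on MIP, on walking and cough function, and on the 1-year respiratory complications. If the arms do differ in exposure, the treatment estimate carries part of the exposure effect, and readers will ask for an adjusted result that was not prespecified. Choosing covariates after an imbalance has been seen is weaker than naming them now.

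The stated reason in Limitations is also wrong. Every two-arm trial assigns by type of treatment. Chance imbalance in a covariate persists because allocation is not stratified on that covariate. The sentence presents a design choice as a consequence of having two kinds of training.

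**Working it through.** **1. The plan's own power figure.** Power Calculations uses "With a total of 80 participants (40 in each group) in this study" and "a 2-sided repeated measures ANOVA comparing 2 treatments across 3-time points", with f = 0.16 and power above 0.8. The symbols before the last two values in that bracket are lost in the text, so I assume two-sided alpha 0.05 and within-person correlation 0.5.
- Noncentrality: λ = f²·N·m/(1−ρ) = 0.0256 × 80 × 3 / 0.5 = 12.288.
- With 2 and 156 degrees of freedom, the critical F is 3.054 and power is **0.885**. The claim of more than 0.8 reproduces. (The printed F = 3.067 fits 2 and 128 degrees of freedom, that is N = 66, where power is 0.811, also above 0.8.)

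**2. Do unequal arm sizes matter?** Suppose allocation were a coin flip for each of 80 people. The central 95% range for one arm is then 31 to 49. At 31/49, λ is multiplied by 4 × 31 × 49 / 80² = 0.949, giving 11.67 and power **0.867**. Arm size is not the problem.

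**3. How large could the smoke-exposure imbalance be?** The article gives no prevalence, so I take 20%, 30% and 40% of 80. The table shows the standard deviation of the between-arm difference in the exposed proportion.

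| Exposed | Coin flip | Fixed 40/40 list |
|---|---|---|
| 20% (16) | 0.091 | 0.090 |
| 30% (24) | 0.104 | 0.103 |
| 40% (32) | 0.111 | 0.110 |

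Check for the fixed list at 30%: the variance of the exposed count in one arm is 40 × 0.3 × 0.7 × 40/79 = 4.253. Its root is 2.062, and 2 × 2.062/40 = 0.103. Fixing the arm sizes barely changes the imbalance. Only stratification removes it, and only adjustment corrects for it.

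**4. What that does to the MIP comparison.** Let δ be the effect of exposure on MIP that remains after the listed covariates. A difference d in exposure shifts the unadjusted treatment estimate by d × δ. The article gives no δ. As a deliberately high illustration, set it equal to the planned between-arm difference, 18.9 − 9.3 = 9.6 cm H2O.
- One standard deviation of imbalance: 0.091 × 9.6 = 0.9 to 0.111 × 9.6 = 1.1 cm H2O.
- Two standard deviations at 30% exposed: 0.208 × 9.6 = 2.0 cm H2O.
- With δ half as large (4.8), these shifts halve.
- For scale, the standard error of a simple 40 versus 40 comparison is 12.8 × √(2/40) = 2.86 cm H2O.

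**5. What adjustment gains in precision.** Exposure with prevalence 0.3 accounts for a variance of δ² × 0.3 × 0.7. At δ = 9.6 this is 92.16 × 0.21 = 19.4, or 12% of 12.8² = 163.8. At δ = 4.8 it is 4.8, or 3%. The cost is one model parameter.

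**6. What late stratification could still achieve.** Results reports 69 enrolled by July 2024. That leaves 80 − 69 = 11 to reach the powered sample, or 95 − 69 = 26 to reach the enrolment ceiling. Perfect balance among those would cut the standard deviation of the exposed-count imbalance to √(69/80) = 0.93 or √(69/95) = 0.85 of its value, a reduction of 7% to 15%.

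**The case against.** **The case for leaving the plan alone.**
- The smoke objective is exploratory and is meant chiefly to inform a later study.
- The possible imbalance is openly disclosed.
- Chance imbalance under randomisation is not bias over repeated trials; the standard error already reflects it.
- Adjusting for the baseline value absorbs part of the effect that runs through lower baseline function.
- The covariate list could be read as not exhaustive, and a fuller analysis plan may extend it.
- Cotinine reflects only the past 48 hours, so the category is an imperfect measure of exposure history.

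Most of this stands, and it keeps the point small. It does not remove it. The article ties exposure to training tolerance and airway clearance as well as to baseline level, and baseline MIP cannot fully stand in for those. The 1-year respiratory outcome has no evident baseline value to adjust for. The article names age, gender and BMI but leaves out the one factor that it expects may be unbalanced.

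**Stronger readings that the article does not support.**
- A reader might infer that the RAND function means unrestricted allocation. The function can equally sort a fixed 40/40 list or build permuted blocks, and the article does not say which was done.
- A reader might infer that the draw was repeated because the worksheet function recalculates. That is a property of the software; nothing says the values were not fixed.
- A reader might infer selection bias from staff making the allocations. The article does not say who generated or released them, and a condensed article commonly leaves this to the full protocol.
- A reader might say that RAND creates the smoke imbalance. Step 3 shows that a fixed 40/40 list leaves nearly the same imbalance.
- A reader might say that missing 40 per group threatens power. Step 2 shows that it does not.

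**Conclusion.** The concern holds in a limited form. By the article's own account, smoke exposure may differ between arms and is related to function, training tolerance and respiratory health, yet the stated between-arm model omits it. The expected imbalance is about 9 to 11 percentage points (one standard deviation) if 20% to 40% of 80 are exposed. On MIP this is worth roughly 1 cm H2O or less for a typical imbalance, and about 2 cm H2O for a large one, even with a generous exposure effect of 9.6 cm H2O. Prevalence and exposure effect are both assumptions. The effect on the 1-year respiratory outcome cannot be sized from the article.

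The primary comparison remains valid and adequately powered without the change. This is a nearly free improvement to a stated analysis rule, together with a correction to the reasoning in Limitations. It is not evidence of a faulty randomisation.

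**What to change.** - **Statistical Analysis:** add the two-level cotinine category, taken at baseline before training starts, as a covariate in the between-arm models for MIP, the functional outcomes and the 1-year respiratory outcome. Specify this before unblinded data are examined.
- **Limitations:** say that unequal smoke exposure is possible because allocation is not stratified by it, and that the between-arm analysis adjusts for it. Remove the attribution to assignment by training type.
- **Optional:** stratify any remaining allocations by cotinine category. The benefit is limited (7% to 15%, step 6), and the cotinine result would have to be available before allocation.

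Cost: one added covariate from data already planned for collection, and one reworded sentence. It applies to all participants, including those already enrolled, provided their cotinine result dates from baseline. The article does not state the timing of the test, so this should be confirmed.
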